#### Time schedule

The duration of the entire project is 36 months (December 2010 to November 2013).

The period between recruitment of a GP and patient screening at the GP's practice should ideally not exceed 8-10 weeks. For this reason, recruitment of GPs is performed in stages. Recruitment of GPs starts in August 2011 and ends in December 2012.

Recruitment of participants starts in January 2012 and ends in March 2013 (15 months). The last participant is expected to finish the intervention in June 2013. Altogether, the period between "first patient in" and "last patient out" is 18 months.

### Experimental and control intervention

#### Overview

The experimental intervention has been designed according to state-of-the-art physical activity recommendations for older adults [7]. It consists of:

1. multidimensional (strength, endurance, balance, flexibility) home-based exercise integrating preventive and therapeutic recommendations

2. consultations provided by an exercise therapist (at the GP's practice and via telephone) including personal attention, instruction, and methods fostering behavioural change.

The control intervention promotes baseline physical activities [[57], page 2], and thus consists of:

1. baseline activities of daily life, e.g. light-intensity walking,

2. consultations provided by an exercise therapist (at the GP's practice and via telephone) including personal attention and instruction.

The duration of the intervention is 12 weeks (see Figure 2). The exercise therapist provides a given number of personal consultations at the GP's practice (weeks 1, 2, 4, 7, 11) and a given number of consultations on the telephone (weeks 5, 8 and 12). If the participant misses an appointment, a new appointment is scheduled within the following days or weeks (as soon as possible).

**Figure 2 F2:**
[figure not shown]
**Time schedule of the intervention**.

#### Common aspects for both groups

Any additional medical treatment is permitted before and during the trial, with the exception of on-going rehabilitation measures following an inpatient surgical procedure (see exclusion criteria).

The exercise therapist will inform the GP about the initial assignment and further development of his/her patients in order to enable the GP to encourage and support his/her patients during normal office visits.

In order to ensure that both groups receive a similar amount of personal attention, the control group receives the same number of consultations at the GP's practice and via telephone as the experimental group (see Figure 2).

#### Experimental intervention details

Development and content of the experimental intervention have already been extensively discussed and presented in the study protocol of the feasibility study [53]. Therefore, the following descriptions are limited to information on modifications of the programme (based on results of quantitative and qualitative analyses) and additional background that has not yet been presented in detail (e.g. aspects on behaviour change).

##### Home exercises

Analysis of correctness of exercise performance revealed that some exercises were less appropriate than others, or were only performed by a small percentage of participants [58]. These exercises have been replaced by more suitable ones. An overview of the chosen exercises is given in Table 2.

**Table 2 T2:** Overview of home-exercises

Category	**No**.	Exercise (variants)
**Strength**	**1**	Knee extension (seated/standing)
	
	**2**	Leg abduction (standing)
	
	**3**	Calf-raise (standing)
	
	**4**	Biceps curl (seated/standing)
	
	**5**	Upper back (seated/standing)
	
	**6**	Seated crunches

**Flexibility**	**7**	Seated sit-and-reach
	
	**8**	Upper back and chest stretch (seated/standing)

**Balance**	**9**	One-leg-stand
	
	**10**	Tandem stand (tandem walk)

##### Consultation sessions

Table 3 presents the eight sessions of the multidimensional home-based exercise programme. Each session has a certain topic matched with the mode of consultation. Face-to-face consultations deal with the topics "Getting started", "Strength", "Endurance", "Balance", and "Flexibility". In these sessions, participants practise the accurate performance of exercises after considering why and how they should exercise. Telephone consultations cover "Barriers and resources to physical activity", "Physical activity and specific medical conditions", and "Living an active life".

**Table 3 T3:** Overview of the 12-week experimental intervention: the HOMEfit exercise programme

**Session no**.	1	2	3	4	5	6	7	8
**Intervention week no**.	1	2	4	5	7	8	11	12

**Type of contact**	face-to-face	face-to-face	face-to-face	by telephone	face-to-face	by telephone	face-to-face	by telephone

**Main topic**	**Getting started**	**Strength**	**Endurance**	**PA and specific medical conditions**	**Balance**	**Barriers and resources to PA**	**Flexibility**	**Living an active life**

**Beginning**	Motives for participation Current PA behaviour and exercise biography	Identification of state of health and feeling Action control-Reflection of the previous week(s) Clarification of session topic						

**Theoretical part**	General health benefits of PA, recommendations for health-enhancing PA Goal setting for the end of the intervention The programme, organisational aspects Begin exercising-hints and safety tips	Significance of strength for health and everyday life How to improve strength	Significance of endurance for health and everyday life How to improve endurance	Benefits of PA for prevention and treatment of a specific medical condition, e.g. coronary heart disease, diabetes, or arthritis (according to patient's choice)	Significance of balance for health and everyday life (fear of falling) How to improve balance	Identification of individual barriers and resources to physical activity (significance of social support) Strategies for dealing with barriers	Significance of flexibility for health and everyday life How to improve flexibility	Lifestyle PA Staying physically active Falling back into inactive behaviour

**Practice**	Body perception: Active standing Warm-up programme	Warm-up programme Strength exercises	Warm-up programme Short walking session outside		Warm-up programme Balance exercises		Warm-up programme Flexibility exercises	

**Conclusion**	Goal setting and action planning for the following week	Goal setting and action planning for the following two weeks	Goal setting and action planning for the following week	Goal setting and action planning for the following two weeks	Goal setting and action planning for the following week	Goal setting, action planning and coping planning for the following three weeks	Goal setting, action planning and coping planning for the following week	Goal setting, action planning and coping planning for the near future

PA = physical activity

##### Changing physical activity behaviour

As initially stated, the experimental intervention is based on the Health Action Process Approach (Schwarzer et al.) in order to foster patients' behavioural change. In the following sections, the essential elements of HAPA are briefly introduced, directly followed by a paragraph (→) describing how the respective element is considered in the intervention.

As a continuous model, HAPA suggests a distinction between motivational processes that lead to a behavioural intention and volitional processes of goal pursuit that end with successful performance. As a stage model, the behaviour change process subdivides individuals into non-intenders, intenders, and actors. Non-intenders do not have the intention to change their behaviour; they need to be motivated (motivational phase). Intenders have formed an intention but have not yet started to act; they require skills to translate their intention into action (volitional phase). Actors have already started to implement their intention; they need assistance to maintain their initiated behaviour (volitional phase). For details, see Schwarzer et al. [54]. The stage version intends to deliver starting-points for interventions.

→ In the experimental intervention, we adopt the HAPA model as follows: patients who give their written informed consent to participate are considered as individuals with an intention to change their physical activity behaviour, even though this intention may be weak. Therefore, the experimental intervention aims at:

(a) strengthening participants' motivation and thus the intention to exercise, and

(b) assisting intenders and actors in improving their volitional execution skills to adopt the exercise programme and to maintain the new behaviour, respectively.

Non-intenders are not considered in this study.

##### Motivational elements

An intention is considered to be the basic precondition for a behavioural change and has been shown to be associated with physical activity behaviour [59,60]. According to Schwarzer et al. [54], perceived self-efficacy and outcome expectancy are the two major components influencing the formation of an intention. The significance of outcome expectations and in particular, perceived self-efficacy for physical activity behaviour has been proved in a number of studies in healthy or chronically diseased (older) adults [61-69].

###### Self-efficacy

A person's confidence in his/her ability to perform a particular behaviour under various circumstances is called self-efficacy. It is considered to be the basis for all human motivation and action [70]. Self-efficacy is thus a core element of many behaviour change models and a basic construct throughout all phases of the HAPA [54].

There are certain strategies for positively influencing an individuals' belief in his/her competence to increase physical activity and to exercise. Lee et al. [64] present sources of self-efficacy beliefs that have proved to be useful in exercise interventions for older adults:

a) Performance accomplishments: the experience of success strengthens an individual's self-efficacy, while negative experiences weaken the belief in one's own abilities. Performance accomplishments are suggested to have the strongest impact on perceived self-efficacy. Particularly for older adults, it has been proposed to set achievable subgoals allowing for gradual progress.

b) Vicarious experience: "People with a comparable lifestyle [...] or those with similar characteristics [...] may serve as models for a specific behaviour and necessary skills. This may be a particular issue for older people where a lack of role models within a similar age group may reinforce the belief that exercise is irrelevant" [[64], page 1694]. For successful vicarious learning, a role model chosen for an older adult must be comparable with the subject. Seeing this role model exercise may strengthen the older person's belief in his/her own capabilities to perform equal activities.

c) Verbal encouragement: giving realistic positive feedback is a further strategy for increasing perceived self-efficacy. Encouragement from health care professionals has been shown to be particularly motivating among older adults. Interventions that used both telephone and face-to-face encouragement to support older people in regular walking as exercise significantly increased participants' exercise self-efficacy and self-reported amount of walking [71,72].

d) Perceived physiological and affective responses: exercising is accompanied by specific physiological and emotional responses that may be positive (e.g. vitalisation-enjoyment) or negative (e.g. fatigue, breathlessness, pain-stress, fear). Exercise interventions for older adults should enable the experience of positive physical and mental states and avoid physical overexertion and mental stress in order to promote self-efficacy beliefs and in so doing, foster the motivation to exercise. Older adults in particular may perceive non-hazardous physical symptoms (e.g. muscular fatigue) as signs of vulnerability. These older adults have to be assisted in reinterpreting what they perceive as health-threatening symptoms.

###### Outcome expectancy

Outcome expectancy is defined as the expectation of positive and negative outcomes that follow the accomplishment of a certain action [73]. Regarding exercise, such expectations may refer to physiological and affective responses, reactions from the social environment or (dis)satisfaction with the performance. Outcome expectations may be based on positive and negative experiences, a lack of experience, or attitudes towards exercise and physical activity. Firstly, interventions for older adults should aim at increasing the awareness of the multifaceted positive health outcomes of exercising in old age. Secondly, it is necessary to enable positive and avoid negative experience of physical activity (see strategy d) above). For details, see Williams et al. [73].

→ Implementation in the intervention: the overriding goal of each session of the experimental intervention is to positively impact perceived self-efficacy and outcome expectancy concerning physical activity and exercise. The individuals' motives for participation are discussed at the beginning of the first session. With regard to outcome expectancy, exercise therapists discuss the benefits of physical activity for health in general and for a specific medical condition (according to the patient's choice from a given set of medical conditions; session nos. 1, 4), and highlight the significance of physical competence (strength, endurance, balance, flexibility) for autonomous mastery of everyday life (session nos. 2, 3, 5, 7; see Table 3). The following sources are provided to increase participants' exercise self-efficacy: (1) exercise therapists tailor the programme to the individual capacities and needs of each participant (not only on the physical but also on the cognitive level) to avoid excessive demands and facilitate the experience of success; (2) throughout all sessions, exercise therapists listen with empathy and encourage participants; (3) a role model (older adult in street clothes performing the exercises of the programme) is shown in the illustrated workbook (see below: *Materials*). All these elements aim at increasing the motivation to perform the home-based exercise programme.

##### Volitional elements

In addition to strengthening the motivation to exercise, participants are assisted with strategies that facilitate the translation of their intention into action. Goal setting, strategic planning (action planning and coping planning) and action control have been shown to be effective self-regulatory skills that are particularly important in the first weeks of trying to overcome a sedentary behaviour. This also applies to older adults [54,59,60,74-79].

###### Goal setting

Setting a goal leads to a "sense of commitment that obligates the individual to realize the goal" [[80], page 494]. Proximal and specific goals result in better implementation than distal and vague goals. For details see the review of Gollwitzer [80].

→ Implementation in the intervention: at the beginning of the intervention, the exercise therapist clarifies the distal goal for the end of the intervention, which ideally corresponds to the physical activity recommendations. To increase and maintain participants' exercise self-efficacy, the distal goal is broken down into achievable subgoals. At the end of each session, participants are assisted in individually setting proximal goals for the next (two/three) week(s) of the intervention, e.g. performance of specific exercises on one day, walking for 15 minutes as exercise on two days of the following week (see Table 3).

###### Action planning

In "action plans", people define where, when and how they will perform a certain action. This leads to a more or less "automatic" initiation of the intended behaviour when the predefined situation occurs [54]. Action plans foster goal attainment by helping people get started [80].

→ Implementation in the intervention: action planning is a basic element at the end of each session of the intervention (Table 3). Participants plan on which days and at what time they will either go walking as exercise or do their strength, balance and flexibility exercises.

###### Coping planning

After people specify when, where, and how they intend to attain their goals, they need to anticipate possible barriers and to develop coping strategies [54]. Combined action and coping planning has been shown to be even more effective in increasing physical activity than action planning alone [76,78].

→ Implementation in the intervention: coping planning is addressed as a central topic of session no. 6 (see Table 3). During the telephone consultation, participants identify the individual barriers that prevent them from performing the planned exercises. Subsequently, they generate strategies to overcome these barriers. Coping plans are added on top of action plans at the end of session nos. 6 to 8.

###### Action control

"Self-monitoring is essential in action control as long as a behaviour has not become a habit. To control their behaviour individuals must monitor their actions to evaluate whether they are on track [...]" [[60], page 89].

→ Implementation in the intervention: patients are asked to fill out an activity log every evening. They record duration of walking as exercise, performance of home exercises, total step count (each participant gets a pedometer that displays daily step count on a screen), and comments (e.g. reasons for inactivity, problems with certain exercises). This self-monitoring facilitates matching of action plans and actual performance of the exercise programme. Additionally, it provides the basis for possible adaptations of exercises to individual requirements in the course of the programme. The activity log is discussed at the beginning of consultations during the reflection on the previous week(s) (see Table 3).

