##### Consultation sessions

Table 4 presents the eight sessions of the control intervention. The topics discussed in the initial face-to-face consultation are similar to the first session of the experimental intervention. During the second face-to-face session, exercise therapists discuss participants' daily routines with regard to their physical activity and sedentary behaviour. During the final personal consultation, participants once again reflect about their daily routine and current physical activity level compared to the level at the beginning of the study. The two blocks of personal and telephone consultations in between are dedicated to the discussion of opportunities for increasing baseline activity at home and in public, and implementation, respectively. Finally, participants are counselled by phone with regard to staying active in daily life.

**Table 4 T4:** Overview over the 12-week control intervention

**Session no**.	1	2	3	4	5	6	7	8
**Intervention week no**.	1	2	4	5	7	8	11	12

**Type of contact**	face-to-face	face-to-face	face-to-face	by telephone	face-to-face	by telephone	face-to-face	by telephone

**Beginning**	Motives for participation	Identification of state of health and feeling						

**Topics**	Current PA behaviour and exercise biography General health benefits of PA Baseline PA The programme, organisational aspects	My daily routine and physical (in)activity	Opportunities for increasing baseline activity at home	Implementation of baseline activities at home	Opportunities for increasing baseline activity in public	Implementation of baseline activities in public	My daily routine and physical (in)activity: before and today	Staying physically active Falling back into inactive behaviour

PA = physical activity

There is no goal setting or strategic planning in the control intervention. Exercise therapists focus on giving information and instructions.

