##### Materials (control intervention)

Each participant receives a booklet containing information on the benefits of physical activity for health and everyday life, opportunities to integrate more baseline physical activity into the daily routine, and on how to keep up. Participants receive no further materials.

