#### (Serious) adverse events

During every encounter with the participant (either experimental or control intervention group), the exercise therapist assesses and documents all adverse events (AEs, any previously unknown or increasing symptom or disease of any participant) by a standardised report protocol. The therapist forwards all protocols with AEs (the same day, personally or via fax) to the GP, who judges: serious/not serious; related/not related to participation in the study; subject may not continue participation/subject may continue participation but has to pause completely for x days/subject may continue participation immediately but with restrictions for x days/subject may continue participation immediately without any restrictions. Adapting the ICH Guidelines on "Clinical Safety Data Management-Definitions and Standards for Expedited Reporting E2A" [112] to our intervention, a serious adverse event (SAE) is defined as "any untoward medical occurrence that [...] results in death, is life-threatening, requires inpatient hospitalisation [...]" or "results in persistent or significant disability/incapacity [...]".

Outcome assessors report SAEs to the GP on the same day, if they obtain the information during assessments at the practice.

SAEs are also independently reported by the GP using the standardised report protocol immediately after he/she obtains knowledge of them during routine consultations at the practice or via other information routes.

Protocols of adverse events that have been classified as "serious" by the GP are forwarded promptly by fax (secure receipt) to the SAE manager (who is affiliated to the Institute of General Practice and Family Medicine, University of Witten/Herdecke), who reviews the GP's judgements. AE protocols remain at the practice for monitoring purpose.

The Institute of General Practice and Family Medicine (University of Witten/Herdecke) collects all SAE protocols, analyses frequency and type of SAEs and provides summary reports to the Data Safety and Monitoring Board (DSMB) on a regular basis. In case of numerous occurrences of SAEs, the DSMB suggests that the study should be stopped.

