##### Patient compliance, appraisal by participants and by GPs, (S)AEs, discontinued participation

Patient compliance, appraisal by participants and by GPs, (S)AEs, and discontinued participation are analysed descriptively and presented per group (experimental vs. control).

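### Extra prompts in the experimental arm put the by-arm table of non-serious adverse events at risk of unequal ascertainment

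*Protocol article*

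**What the plan says.** **Recording.** Under (Serious) adverse events, at every encounter in either arm "the exercise therapist assesses and documents all adverse events (AEs, any previously unknown or increasing symptom or disease of any participant", using a standardised form. Methods to prevent bias states that therapists and GPs know the allocation. Under Statistical analyses, adverse events "are analysed descriptively and presented per group (experimental vs. control".

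**Experimental arm.** Under Action control, "patients are asked to fill out an activity log every evening". Its contents include "comments (e.g. reasons for inactivity, problems with certain exercises". The same section adds: "The activity log is discussed at the beginning of consultations during the reflection on the previous week(s". On the face-to-face consultations the article says: "In these sessions, participants practise the accurate performance of exercises after considering why and how they should exercise". Table 3 has a practice entry for each of the five face-to-face sessions.

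**Control arm.** Under Materials, participants get a booklet, and "Participants receive no further materials". Under Consultation sessions, "There is no goal setting or strategic planning in the control intervention". Table 4 has no practice row and no review of past weeks under its opening item.

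**What is matched.** Both arms have eight contacts in the same weeks, five in person and three by telephone. From session 2 on, both session tables open with an enquiry about the participant's health and how he or she feels.

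**The concern.** Equal contacts equalise the occasions for reporting. They do not equalise what triggers a report. The therapist who reads the log and watches the exercises is also the person who completes the adverse-event form, and does so unblinded. The definition is broad enough that a log remark about new or worse knee pain as a reason for not exercising would qualify. A control participant with the same pain is asked about health at the same visits but has no written daily record to bring it up.

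The feasibility study had a single arm, so this trial's control group supplies the concurrent background rate of symptoms. In chronically ill people aged 70 or over that background can be expected to be substantial, and a by-arm table exists to set it apart from programme effects. If symptoms are elicited unequally, part of any difference in non-serious events could be an artefact of elicitation, and readers will still take a descriptive table as a safety comparison.

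**Working it through.** **1. The plan's own figures.** The article gives no adverse-event rate, so there is no safety figure to reproduce. Its only design calculation is the power of the primary ANCOVA. A 10,000-run simulation of the listed steps (15 centres of 14, centre effect added to both time points as an assumed reading) gave 94.0% against the stated 94.6% at correlation 0.78, and 87.2% against 86.7% at 0.70. The present point does not bear on that calculation.

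**2. Prompts side by side.**

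| Feature | Experimental | Control |
|---|---|---|
| Contacts with therapist | 8 | 8 |
| Gaps between contacts (weeks 1, 2, 4, 5, 7, 8, 11, 12) | 1 to 3 weeks | 1 to 3 weeks |
| Health enquiry in session table | from session 2 | from session 2 |
| Standardised form | yes | yes |
| Evening log | at most 12 × 7 = 84 entries | 0 |
| Log review with therapist | yes | no |
| Face-to-face sessions with practice | 5 | 0 |
| Telephone session on barriers to activity | session 6 | none |
| Telephone session on a chosen medical condition | session 4 | none |

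The first four rows are balanced; the last five are not. The 84 is a count of log days, not of events.

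**3. What unequal capture would do.** Let p be the true share of patients with a non-serious event, equal in both arms, and c0 and c1 the probabilities that such a patient is recorded in the control and experimental arms. All three are assumptions.

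- Recorded patients per arm: 105 × p × c.
- Recorded ratio: c1/c0, which does not depend on p.
- Spurious difference in shares: p × (c1 − c0).

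| c0 | c1 | Ratio | Recorded at p = 0.4 (control vs experimental) | Difference for p = 0.2 to 0.6 |
|---|---|---|---|---|
| 0.8 | 0.8 | 1.00 | 33.6 vs 33.6 | 0 |
| 0.8 | 0.9 | 1.125 | 33.6 vs 37.8 | 2 to 6 points |
| 0.6 | 0.9 | 1.50 | 25.2 vs 37.8 | 6 to 18 points |

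For example, 105 × 0.4 × 0.9 = 37.8 and 105 × 0.4 × 0.6 = 25.2. The first row matters as much as the others: if the enquiry common to both arms already captures events equally, there is no artefact.

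**4. Serious events.** The GP reports these independently of the therapist, and blinded outcome assessors pass on any they learn of at assessments in the practice. These routes do not run through the log or the practice sessions. The GP who judges seriousness and relatedness does know the allocation.

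**The case against.** The strongest case against is that the plan already requires active assessment of adverse events at all eight contacts in both arms, on one form. A reader might infer that controls depend on unaided recall; the article does not support that. The health enquiry appears in both session tables, and in Table 3 it is listed ahead of the log review, so a common question before the log is at least indicated. Control sessions also discuss daily routine and how activities are put into practice, which may bring out complaints.

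The log is described as a tool for self-monitoring and for adapting exercises, and nothing routes its entries to the adverse-event form. The form's fields are not reproduced, and the article refers to manuals and further documents, so one cannot say that the source of a report goes unrecorded, only that no source field is described. A symptom provoked by supervised exercise is a real effect of the programme; only the greater chance of noticing it is an ascertainment matter. The analysis is descriptive, so no test or error rate is at stake.

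All of this stands. It rules out claiming that bias occurs. It does not remove the imbalance in prompts, because a shared form and a shared opening enquiry leave the log review and the observed practice as additional triggers in one arm, in front of an unblinded recorder.

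**Conclusion.** The point holds as a risk, not as a demonstrated bias. The table of non-serious adverse events per arm is open to differential ascertainment, most plausibly against the exercise programme. The direction is not certain: the Self-efficacy section says older participants should be helped to reinterpret sensations they see as threatening, which could reduce reports in the same arm.

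A reader might conclude that the table is biased, and by a known amount. The documents do not support either step, since they contain no event or capture rates. The ratios of 1.125 and 1.50 rest wholly on assumed capture probabilities, and 1.00 is equally compatible with the text. Serious events are little affected, and the primary analysis is untouched. This is a cheap improvement that makes the safety comparison interpretable; it does not correct an error.

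**What to change.** - **(Serious) adverse events:** have the therapist ask one identical scripted question about adverse events in both arms at the start of every contact, before the log is reviewed and before any practice. Record the source of each event: scripted question, log, observed in session, or other. This also settles whether log entries count as a source. Same-day reporting to the GP stays as written.
- **Statistical analyses, section covering (S)AEs:** keep the all-source count per arm as the main table. Beside it, show the count from the scripted question alone and a breakdown by source, with serious events separate. The scripted-question count should not replace the all-source count, because that would drop real harms seen in practice sessions or found only in the log, and so favour the programme.

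The cost is one question, one form field and one extra table split, with no added visits or staff. It has to be in place before data are collected; the article states that recruitment of participants had not begun at submission.
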